#### Recruitment and eligibility criteria

Based on the sample size estimate, this study is intended to recruit 24 classes from six primary schools (grades 2–5), excluding the private or special education schools or those participating in other PA-related programs. Using a random stratified sampling approach (e.g., socioeconomic status, geographical location, grade and class size of each school), six primary schools will be recruited in Shijiazhuang, Hebei, China. An invitation letter describing the study nature and participation requirement will be delivered to the principals of eligible schools. Upon the approval of the principals, one class from each grade will be randomly selected to participate in this study. All children in the selected classes will be provided with an informed pack comprising a plain language statement and a written informed consent form to be signed by their parents. The eligibility criteria will include: (1) aged 8–12 years; (2) Body Mass Index (BMI) greater than Chinese obesity cutoffs corresponding to 95th percentile of sex-specific and age-specific BMI reference standards [62]; (3) no previous substantial experiences in participating in FMSs-related promotion programs; (4) no prior diagnosis of physical, verbal, and cognitive disorders that may prevent participation in PA program and interrupt the outcome evaluation.

#### Randomization and blinding

To avoid the potential for contamination, randomization will be conducted at the school level. All eligible schools will be randomly assigned to one of the two groups prior to baseline assessment, where each group will consist of three schools. Each school will select 28 obese children from four classes covering grades 2–5 to participate in this study, and the children in the same school will receive the same treatment. Randomization will be implemented with a ratio of 1:1, using the Excel software by a researcher who will not be involved in the participant recruitment, data collection or evaluation. Due the ethical concerns, participants are not able to be blinded as they will be informed with the study purpose and group allocation in the written informed consent form. Intervention facilitators and outcome evaluators will be concealed for the group allocation.

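### The group is disclosed at consent and no rule governs which 28 children a school enters, so recruitment can differ between arms after allocation

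*Protocol article*

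**What the plan says.** Under Randomization and blinding, the protocol article makes the school the unit ("randomization will be conducted at the school level"), with three schools per group, and places allocation early: "All eligible schools will be randomly assigned to one of the two groups prior to baseline assessment". Participants cannot be blinded, it explains, because "they will be informed with the study purpose and group allocation in the written informed consent form". On entry of children it says: "Each school will select 28 obese children from four classes covering grades 2–5 to participate in this study". It gives no rule for that selection.

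The stated safeguards are these:
- Randomisation is done "by a researcher who will not be involved in the participant recruitment, data collection or evaluation".
- "Intervention facilitators and outcome evaluators will be concealed for the group allocation".
- Under Recruitment and eligibility criteria, "one class from each grade will be randomly selected to participate in this study", and every child in a selected class receives the information pack and consent form.

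The abstract's Methods paragraph puts the steps the other way round, with recruitment before assignment. Data analysis plans a mixed model adjusted for baseline values, and baseline tests to detect possible confounders.

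**The concern.** In a cluster trial, randomisation balances the schools. It balances the children only if their entry does not depend on the arm. Here the people who decide on entry, parents and schools, can know the arm when they decide.

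The two offers are very unlike. Intervention families are offered a 24-week programme. It has 12 weeks of school sessions plus family assignments at least three times a week with weekly uploads and prizes, then 12 weeks of workshops and webinars attended with a parent. Waiting-list families get nothing until all data are in, at 48 weeks, yet face the same four assessment rounds of ten days each. Families who accept one offer need not resemble those who accept the other in motivation, parental support or fitness.

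Children also perform the baseline tests knowing their group, so the covariate used for adjustment is not fully protected. What is at stake is the primary comparison. A difference in who enters would look like an effect of the programme, or would hide one.

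**Working it through.** **1. Order of steps.** Randomization and blinding says only that allocation precedes baseline; it does not say that it precedes recruitment. The same section has the consent form state the allocation. A form can do so only if allocation is already fixed when it is signed. Allocation therefore precedes enrolment, and the abstract's order does not fit. If the abstract is right, the consent sentence is wrong and needs correcting.

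**2. What each safeguard covers.**
- Independent randomiser: protects generation of the allocation, not enrolment after it.
- Random choice of classes and packs for all children: prevent choosing classes, not differential consent within a class.
- Concealment: covers facilitators and outcome evaluators. Parents are told the group, and nothing is said about the school staff who select children.

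**3. Room for selection.** The quota fits the planned total: 6 schools × 28 = 168, or 3 × 28 = 84 per group. Sample size estimate gives a minimum class size of 30 and an obesity prevalence of about 20%. Expected obese children per school = 4 classes × class size × 0.20.

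| Class size | Expected per school | Probability of at least 28 (binomial) |
|---|---|---|
| 30 (plan's minimum) | 24 | 0.21 |
| 35 (assumed) | 28 | 0.53 |
| 40 (assumed) | 32 | 0.81 |
| 50 (assumed) | 40 | 0.99 |

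These counts are before refusals and exclusions. Classes must average 28 / (4 × 0.20) = 35 for 28 to be expected. At the minimum size the expected number falls short (24 against 28), so there is little to choose from and the numbers depend on consent. At 40 to 50 per class, about 4 to 12 children per school would be left out, by no stated rule.

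**4. What a bias could do (illustration).** The document gives no size. Assume no true effect and a prognostic difference of b SD between arms left after adjustment. Take 84 per arm, the plan's ICC of 0.01, outcome SD 1 and a normal approximation.

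SE = √[(2/84) × (1 + (m − 1) × 0.01)]

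Type I error = Φ(b/SE − 1.96) + Φ(−b/SE − 1.96)

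With m = 6 (class as cluster), SE = √(0.02381 × 1.05) = 0.158. With m = 28 (school as cluster), SE = √(0.02381 × 1.27) = 0.174.

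| Assumed b | m = 6 | m = 28 |
|---|---|---|
| 0 | 5% | 5% |
| 0.1 | 10% | 9% |
| 0.2 | 24% | 21% |
| 0.3 | 48% | 41% |

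Against the planned effect of 0.54 SD, b = 0.1 is 0.1/0.54 = 19% and b = 0.2 is 37%.

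**The case against.** The strongest reply is that the plan has real safeguards and that several tempting readings go beyond the text.

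- **Unblinded baseline measurement.** A reader might infer that T0 is measured by people who know the group. The article states that evaluators are concealed. Only the performance of T0 by children who know their group is supported. Whether concealment would hold is a separate doubt, since PE teachers deliver the sessions and also assist at assessments.
- **Schools picking favourable children.** This is inference. Read with the recruitment section, the word select may be loose wording for a quota, and at minimum class size there is little to choose from. What stands is that no rule is stated.
- **Motivation unmeasured.** It is partly measured. Intention, attitudes, perceived capability and parental support are collected at all four occasions, including T0, and baseline tests look for confounders. So adjustment may help. However, the article does not say that detected confounders enter the model, the answers are given with the group known, and a non-significant baseline test does not show balance.
- **A contrast of 24 weeks of training with a wait.** Training sessions last 12 weeks. They are also given to whole classes, which may narrow the difference in incentive to consent. It need not remove it, because the workshops and webinars are for the obese children only.
- **Three schools per arm as the cause.** Differential consent would be no easier to separate from an effect with many schools. The small number of schools is not part of this point.

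None of these replies reaches the core: parents consent with the group named, and selection of the 28 has no rule.

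**Conclusion.** The point holds as a risk built into the order of steps, not as a demonstrated bias. That consent is given with allocation known follows directly from the article's own sentence on the consent form. That a school could choose among children depends on having more than 28 eligible, hence on classes averaging above about 35 at 20% prevalence, and more once refusals are counted.

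The size and direction of any bias cannot be derived from the document. The type I error figures rest wholly on the assumed residual differences and are not evidence of size. The point deserves action because it touches the primary comparison, later analysis may not fully repair it, and it is cheap to prevent before recruitment.

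**What to change.** - Use one consent form that describes both possible groups without naming the child's.
- Obtain consent and complete T0 in all six schools. Only then should the independent researcher release the allocation, with families told before the programme starts. Disclosure to families is kept; only its timing changes.
- Replace selection of 28 by each school with enrolment of every eligible, consenting child in the randomly selected classes. If a cap is needed, the independent researcher draws the children at random before release.
- Report the numbers eligible, approached and consenting by school and arm.
- Bring the abstract and the Randomization and blinding section to the same order of steps.

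The cost is an ethics amendment for the consent text and a later delivery briefing for facilitators, now one month before the start. That briefing must follow release and be held for intervention schools only. Giving it in all six schools would train control-school teachers in the programme and risk the contamination that school-level randomisation is meant to avoid. The evaluators' training reveals no allocation and can stay before T0. The start may slip by some weeks. Because T1 and T2 are counted from baseline, the plan should say how a longer gap between T0 and the start is handled.

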## Method

### Study design

This study will apply a two-group double-blinded cluster randomized controlled trial (CRCT) with four measurement occasions, including baseline assessment (T0), mid-intervention assessment (T1: 12 weeks after the baseline assessment), post-intervention assessment (T2: 24 weeks after the baseline assessment), and follow-up assessment (T3: 48 weeks after the baseline assessment). Two groups include: 1) an intervention group (IG), receiving the FMSPPOC intervention for 24 weeks; and 2) a waiting-list control group (WCG), receiving the FMSPPOC intervention or relevant materials (based on participants’ requirements) after the completion of all data collection for IG (see Fig. 1). The design, implementation, and reporting of the FMSPPOC will follow the SPIRIT guidelines and the CONSORT statement [54, 55] (Supplement Material 1). The study protocol was approved by the Research Ethics Committee of Hebei Normal University (ref. No.2021LLSC051). This study was a key part of a large research project funded by the National Social Sciences Funding Committee of China (Ref. No.: 19200526).

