**Fig. 2 Fig2:**
[figure not shown]
Gantt chart of research activities

For the project implementation, two 60-min face-to-face briefing sessions will be first provided for the intervention facilitators (i.e., PE teachers, student helpers, parents) one month prior to the FMSPPOC commencement (delivered by the investigators and/or research assistant) in the university gymnasium. One briefing session will focus on necessary knowledge and skills training so that PE teachers and student helpers can implement the intervention plan smoothly and effectively. In addition, the implementation details, rationale, nature, and benefits of FMSPPOC will be introduced. Another briefing session will train all evaluators on the measurement of FMSs, health behaviors, and physical fitness, as well as the specification of psychological measures.

For the main study, the school-based PA sessions will be conducted in an indoor playground at a primary school during afternoon custody time (4:00–5:00 p.m.) by qualified PE teachers with assistance of student helpers. The attendance of participants will be also recorded. In addition, to monitor the PA intensity, three mid-tests will be conducted using downloadable, wireless Polar Team Pro (Polar Team Pro, Kempele, Finland) and Polar heart rate sensor during the ball games (week 3, 7, & 11).

For the family-based PA assignments, relevant tasks and instructions will be introduced for parents in the beginning briefing session. The research assistants will remind parents to upload the required information each week via SMS messages and deliver the incentives correspondingly. For the second 12-week maintenance phase, the offline workshops will be implemented at a multi-function sports room in a primary school, while the online webinars will be conducted using Ding-Talk APP. These workshops and webinars will be facilitated by trained PE teachers and health experts from Hebei Normal University. Each participant will be asked to attend the workshops and webinars with at least one parent or legal guardian.

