**Additional information**	
Demographics	Children’s age, gender, grade (primaries 1–6), ethnicity (Han or others), parental educational level (below college; college or above) and yearly household income (low: RMB < 84,000; medium: RMB 84,000 – 132,000; high: RMB > 132,000) [60] will be reported by parents

In addition, the collection of all indicators at the four-time points will follow the following process. Day 1–7: Demographic information (filled by parents) and ActiGraph 3X + measured PA, sedentary behavior, and sleep; Day 8: anthropometric and body composition measures and FMSs; Day 9: physical fitness assessment; and Day 10: psychological outcomes. The Day 8–10 data collection will be implemented by four trained student helpers with assistance of PE teachers in an elementary school gymnasium, where the temperature will be constant at 20℃ and humidity will be controlled at 50% during the assessment.

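### The double-blinded label and the facilitator-concealment claim contradict the design, and blinding of the TGMD-3 assessors is not secured

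*Protocol article*

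**What the plan says.** All references are to the protocol article.

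- **Study design:** "This study will apply a two-group double-blinded cluster randomized controlled trial (CRCT) with four measurement occasions".
- **Randomization and blinding, on participants:** "participants are not able to be blinded as they will be informed with the study purpose and group allocation in the written informed consent form".
- **Randomization and blinding, on staff:** "Intervention facilitators and outcome evaluators will be concealed for the group allocation". Whole schools are allocated, before baseline.
- **Procedure and quality control, on who the facilitators are:** "briefing sessions will be first provided for the intervention facilitators (i.e., PE teachers, student helpers, parents". The school sessions are run "by qualified PE teachers with assistance of student helpers".
- **Outcome evaluation, paragraph after Table 4:** the Day 8 to 10 "data collection will be implemented by four trained student helpers with assistance of PE teachers in an elementary school gymnasium". The fundamental motor skills, which are the primary outcome, are tested on Day 8.
- **Table 4:** each TGMD-3 criterion is scored by observation as 1 (present) or 0 (absent). For the MABC-2 items the table refers only to the published manual.
- **Abstract, Methods:** the comparator is a waiting list that receives no treatment.

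**The concern.** The article claims a protection that its own procedures rule out for one group and do not secure for another. Facilitators who run or take part in the programme know that their school has it. Assessors are drawn from the same two staff roles, and part of the primary outcome depends on an observer deciding whether a movement criterion was met.

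If an assessor knows the arm and scores more leniently in intervention schools, the leniency follows the treatment and cannot be told apart from an effect. A report that repeated the double-blinded label would lead readers to discount this risk. The Introduction lists lack of blinding among the weaknesses of earlier studies, so the label is also part of the case for this trial.

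**Working it through.** The article gives no figure for this point that could be reproduced. The check sets the statements side by side, role by role, and then adds one illustrative calculation.

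**1. Participants.** They are unblinded by the article's own statement. A double-blinded label would then need two other blinded parties, and the article names facilitators and evaluators.

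**2. Facilitators.** They are PE teachers, student helpers and parents.
- Parents sign the consent form (Recruitment and eligibility criteria), and that form discloses the allocation (Randomization and blinding). One named facilitator group is therefore unblinded on the article's own terms.
- PE teachers, with student helpers assisting, run 2 sessions per week × 12 weeks = 24 sessions of 90 minutes (12-week initiation phase). The control schools receive nothing. Nobody can deliver these sessions without knowing that the school has the programme.

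The facilitator claim fails whoever the individuals are. With it gone, at most one of the two named parties can be blind.

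**3. Evaluators.**

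| Task | Roles named | Section |
|---|---|---|
| Deliver school sessions | PE teachers, student helpers assisting | Procedure and quality control |
| Day 8 to 10 testing | Four student helpers, PE teachers assisting | Outcome evaluation |

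The roles are the same. Procedure and quality control introduces two briefing sessions as being for the facilitators, and the second of these trains all the evaluators. That makes overlap of individuals plausible but does not establish it. No statement keeps the two sets of people apart.

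**4. Room for judgement in the score.** The TGMD-3 maximum in Table 4 can be rebuilt:
- Locomotor: (5 skills × 4 criteria + 1 skill × 3 criteria) × 2 trials = 23 × 2 = 46.
- Ball skills: 54 points over 2 trials = 27 criteria × 2.
- Total: 46 + 54 = 100 present/absent judgements, so one changed judgement moves the total by one point.

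**5. Illustration only.** The article gives neither a TGMD-3 standard deviation nor a rate of misjudgement. Assume an SD of 10 to 12 points and a net 2 to 5 judgements per child flipped in favour of the intervention schools after baseline. Shift in SD units = flips / SD:
- 2 flips: 2/12 = 0.17 to 2/10 = 0.20.
- 5 flips: 5/12 = 0.42 to 5/10 = 0.50.

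Against the planning effect of d = 0.54 (Sample size estimate), these extremes are 0.17/0.54 = 0.31 and 0.50/0.54 = 0.93 of it. The range is too wide to say more than that modest leniency could matter.

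**6. Whether the analysis removes it.** Data analysis adjusts for baseline, so leniency that is constant from baseline onward would largely cancel. Leniency that appears or grows after baseline would not, and neither the intention-to-treat nor the per-protocol analysis addresses it.

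**The case against.** The best defence is that the article names roles and not people. It specifies four student helpers for testing, trains evaluators in a session separate from the implementation briefing, and says that evaluators are concealed. A reader might infer from the shared roles that the same individuals deliver and score. The document does not say so, and the four testers may be different people. This stands: the supportable statement is that separation is not stated. A staff rota is also the kind of detail that a condensed article may leave to a fuller document, so its absence alone would not be a finding. It matters here because the article makes a positive concealment claim and then describes procedures that leave it unsupported.

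Three further limits also stand:
- PE teachers only assist at testing. A reader might infer that they score, but Table 4 does not say who scores and mentions only a trained researcher who demonstrates each skill.
- The argument from observer judgement is shown for the TGMD-3. It should not be extended to the whole primary outcome, because for the MABC-2 items the article refers only to the manual.
- Unblinded participants do not by themselves defeat the double-blinded label, since two other parties are named as concealed. The label fails because the facilitators cannot be concealed.

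None of this rescues the label or the facilitator claim.

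**Conclusion.** The contradiction is established from the text and rests on no numerical assumption. Participants are unblinded, facilitators cannot be blind to a programme they deliver or take part in against no treatment, and the trial is therefore not double-blinded as described. Blinding of the TGMD-3 assessors is claimed but not secured, so detection bias in that score is possible.

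Its size cannot be computed from the document. The 0.17 to 0.50 SD range depends wholly on the assumed SD, the assumed number of flips and the assumption that they all run one way after baseline. A reader might take the upper end to mean that bias could account for nearly the whole planned effect. The article does not support that, because neither input has a source in it. Nor does it show that bias will occur.

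The blinding statements need correcting before the trial is reported. The separation of roles needs settling before outcomes are scored, because live ratings made with knowledge of the arm cannot be repaired in the analysis.

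**What to change.** **Study design and Randomization and blinding.** Delete the double-blinded label and the statement that facilitators are concealed. State that participants and facilitators are unblinded and that only outcome assessors are intended to be blinded.

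**Outcome evaluation, data collection paragraph.** Add three requirements:
1. No student helper who assists in delivery scores the TGMD-3 or MABC-2 at any measurement occasion.
2. Assessors are not told which schools are allocated to the programme.
3. PE teachers marshal the children only and do not score.

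The wording should stay at *intended* to be blinded, because testing takes place in a school gymnasium with children who know their allocation. If the three requirements cannot be ensured, report the assessors as unblinded.

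**Cost.** Changes of wording and a rule on who may score. No extra participants or outcomes are needed. The downside is less flexible scheduling of helpers. The article does not give the total number of helpers, so whether the present team can cover both tasks has to be checked.

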### Fundamental motor skills Promotion Program for Obese Children (FMSPPOC)

FMSPPOC is a school-family blended multi-component intervention program, which aims to promote the development of obese children’s FMSs in a supportive environment, providing the children with both positive experiences (e.g., enjoyment, success, and accomplishment) in relation to PA, and cultivate interest in sports, so as to enhance their PA level/engagement, perceived motor competence, fitness and wellbeing in future. The FMSPPOC will last 24 weeks, consisting of two parts: a 12-week initiation phase, and a 12-week maintenance phase.

